### Concealment mechanism {16b}

The use of opaque sealed envelopes will ensure concealment until the interventions are assigned.

### Implementation {16c}

A member of the research team not involved in the enrolment and investigation processes will generate the allocation sequence using a computer program and seal it in opaque envelopes. The envelopes will be handed over to the investigator who will open them according to the unique sequential number on the envelope at the intervention allocation.

## Assignment of interventions: blinding

### Who will be blinded {17a}

Only the trial participants will be blinded (single-blind). The two treatments taVNS and sham taVNS will be potentially indistinguishable for participants but not for investigators, since both groups will perceive the electrical stimulation even if at two different locations at the ear (concha for taVNS and ear lobe for sham taVNS). The eventual collection of information by the participant on the taVNS method and the correct positioning of the electrode to reach a stimulation of the vagus nerve could lead to a potential unblinding for the participants too.

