### Data management {19}

eCRF entries will be considered source data since the CRF is the site of the original recording (e.g., there is no other written or electronic record of data). In this study, the Qualtrics Survey module will be the eCRF and will be used as the source document for the anamnestic information collected at the screening and for all the assessments and evaluations.

All study data will be entered on the online Qualtrics Survey. Data will be protected in accordance with the “Qualtrics Security statement” (SOC 2 Type II Certification, ISO 27001, 27017, and 27018 Certifications, FedRAMP Authorization, HITRUST), and access available only to the research group. The data will be stored in the online Qualtrics Account owned by to the Principal Investigator (PI) and protected by a unique password.

The participants will be identified by a unique sequential study-specific participant ID number and a unique randomization code. These two numbers will be recorded in the participant module in the IMotions software [32] and on the first page of the online Qualtrics Survey [31]. The name and any other identifying detail will NOT be included in any study data electronic file and no key between participant ID number, name, or other information that could identify the participant will be used. The data recorded in the IMotions software will be stored off-line in a dedicated computer, protected by a password that only the PI has access to.

All the other documents (informed consent, envelope with participant number and randomization code, MINI, and SCID 5 PD) will be stored in a locked cupboard at the lab accessible only to the PI. On all study-specific documents, other than the signed consent, the participant will be referred to by the study participant number/code, not by name.

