## Statistical methods

### Statistical methods for primary and secondary outcomes {20a}

This study constitutes a randomized trial employing repeated measures of a continuous outcome. To address the repeated measures within individuals as delineated by the inclusion criteria (specifically Swedish-speaking females aged 18-50 years diagnosed with BPD), and considering the attendant challenges of collinearity and intra-individual variability, mixed models with individuals as random effects will be employed across various stages of the study (baseline, pre-induction, post-induction, and recovery), as recommended by prior literature [76]. Covariates collected at baseline will be considered, with treatment group, treatment state, and time entered as fixed effects to estimate the effects stemming from the sham/intervention at each time point. The mixed model is versatile, accommodating both continuous and dichotomous outcomes, and will be utilized as deemed appropriate. Given the multitude of potential variables and outcome measures in this study, the necessity for adjustment for multiple tests may arise. To address the issue of multiple testing, we will consider applying the Bonferroni correction, which involves dividing the desired alpha level (typically 0.05) by the number of tests conducted. Alternatively, we may employ false discovery rate (FDR) correction methods to account for the increased risk of false positives when conducting multiple comparisons. The specific method chosen will depend on the final number and nature of outcome measures and variables included in the analysis and will be determined following the completion of the protocol.

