## Oversight and monitoring

### Composition of the coordinating center and trial steering committee {5d}

This is an investigator-initiated study. The PI and research team will collectively manage all aspects of the research process, including protocol development, participant recruitment, data collection, analysis, and reporting. Although there isn’t a designated management team or external steering committee, internal mechanisms have been established to ensure rigorous oversight and adherence to ethical, regulatory, and institutional guidelines.

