### Frequency and plans for auditing trial conduct {23}

In accordance with the nature of this investigator-initiated study, the roles and responsibilities of the coordinating center and trial steering committee are fulfilled by the PI and the research team. The PI assumes leadership in all aspects of the study, overseeing protocol development, participant recruitment, data collection, analysis, and reporting. Internal mechanisms have been established to ensure thorough oversight and adherence to ethical, regulatory, and institutional guidelines. Regular team meetings and protocol reviews facilitate continuous monitoring of study progress and prompt action to address any issues or challenges encountered during the research process.

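### Only participants are masked and the stored randomization code gives away the arm, so the analysis choices still open can be made knowing the allocation

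*Protocol article*

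**What the plan says.** All references are to the protocol article.

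- **Who is masked (section 17a).** The statement is exclusive: "Only the trial participants will be blinded (single-blind"). The reason given is that the two treatments are "potentially indistinguishable for participants but not for investigators", because the electrode sits at a different place on the ear.
- **Who learns the arm (section 16c).** "The envelopes will be handed over to the investigator who will open them according to the unique sequential number on the envelope".
- **Who analyses (sections 5d and 23).** "The PI and research team will collectively manage all aspects of the research process, including protocol development, participant recruitment, data collection, analysis, and reporting". Section 23 repeats this with the PI in the lead, "overseeing protocol development, participant recruitment, data collection, analysis, and reporting".
- **What the records contain (sections 16a and 19).** Participant number and randomization code are entered in iMotions and on the first survey page. Codes 1–21 mean taVNS and 22–42 mean sham. The iMotions data are on an offline computer, "protected by a password that only the PI has access to".
- **What is still open (section 20a).** "Covariates collected at baseline will be considered", without naming any. The choice between Bonferroni and a false discovery rate method is deferred.
- **Who stands outside the sessions (section 16c).** "A member of the research team not involved in the enrolment and investigation processes will generate the allocation sequence".

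**The concern.** The operator has to know the arm in order to place the electrode. Whoever processes the signals, chooses the covariates or settles the multiplicity method does not. Section 17a nevertheless masks nobody but the participant, and its stated reason covers only the operator.

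With 21 participants per arm, whether a prognostic covariate is adjusted for can move the estimated difference noticeably. If such choices are made with the allocation in view, a reader cannot tell whether they were driven by the result, and the reported p-value is harder to take at face value. Arm-aware handling of the ECG and skin-response signals could also colour two supporting arguments: that active stimulation reached the vagus nerve, and that skin response agrees with the self-ratings.

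**Working it through.** The plan states no figure on this point, so the check is mainly textual.

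**1. Does the data file reveal the arm?** Section 16a has the investigator draw a random sequence number from an envelope, with 1–21 meaning taVNS and 22–42 sham. Section 19 stores a randomization code with each record and lists among the stored papers an envelope carrying participant number and randomization code. I therefore read the code as the section 16a number. Anyone who knows the rule can read the arm from the record. Section 16a also records the link between random sequences and study numbers, so deleting the code alone would not be enough.

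**2. Do the people who know the arm also analyse?** The investigator opens the envelope and sees the electrode site. Sections 5d and 23 give recruitment, data collection and analysis to the PI and team collectively. No masked or independent analyst is named.

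**3. Which choices are open?** Section 20a fixes a mixed model with a random effect per participant and with group, state and time as fixed effects. The covariates and the multiplicity method are not fixed. The Trial status section dates the start of recruitment to March 2023. The article, published in June 2024, still leaves both open.

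**4. Which results could be affected?** Section 12 lists only PANAS-N and PEME as primary and secondary outcomes. Both are self-rated by the masked participant in a survey that advances on a timer (section 11a). Skin response serves to validate PANAS-N. Heart rate variability is a stimulation check and an indirect measure of emotion regulation (sections 11c, 12 and 18a). Neither enters the PANAS-N or PEME comparison.

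**5. Would relabelling the arms A and B be enough?** For any covariate set, let b be the estimated group difference and t = b / SE(b). Swapping the labels replaces the group indicator g by 1 − g. Then b becomes −b, SE(b) is unchanged, and the two-sided p = 2·P(T > |t|) is unchanged. The smallest p over all covariate sets is therefore the same whether or not one knows which arm is A. A/B labels stop selection by direction, not selection by significance.

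A null simulation illustrates what such selection can do. It used 3,000 trials, 21 per arm and two-sided alpha 0.05, and took the smallest p over all covariate subsets (2³ = 8 or 2⁴ = 16). It is a single ANCOVA-type comparison, not the planned mixed model, and the number of covariates and their multiple correlation with the outcome are assumptions.

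| Covariates | Multiple correlation | Unadjusted model | Best of all subsets |
|---|---|---|---|
| 3 | 0.3 | 5.7% | 8.7% |
| 3 | 0.5 | 5.0% | 10.7% |
| 4 | 0.5 | 4.5% | 11.5% |
| 4 | 0.7 | 5.4% | 17.2% |

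The simulation error at a true 5% is √(0.05 × 0.95 / 3,000) = 0.4 percentage points. The last column is the result of choosing on the p-value. By the algebra above it would be the same on an A/B file.

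**6. What does remove it?** If the arm column is absent, no group comparison can be computed. Under the null hypothesis, a choice made on pooled data is then independent of the random allocation, so the later test is not selected on its own result.

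**The case against.** The strongest case against has five parts.

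- **The outcomes are protected.** Every primary and secondary rating comes from the masked participant in an automated survey, and no unmasked rater scores anything. This stands. A reader might infer from the single-blind label that the outcome scores are biased by unmasked assessors; the documents do not support that.
- **Nothing says who edits the signals.** A reader might infer that the treating staff clean the ECG and skin-response traces knowing the arm, and that artefact rejection inflates the type I error. The article does not mention artefact handling or say who does it; it gives only the PI's sole access. The signals are not tested outcomes, so their processing cannot change the error rate of a PANAS-N or PEME comparison. This stands.
- **The model type is not open.** The remark in section 20a about using the model as appropriate concerns continuous versus dichotomous outcomes within a stated mixed model. This stands, and narrows the open choices to covariates and multiplicity.
- **A statistical analysis plan may settle these before data are seen, and the team acts collectively.** Both are possible, and one member is outside enrolment and sessions. So the choices can be made knowing the arm; it is not established that they are. But a plan that added a masked analyst would contradict section 17a, so that section needs changing in either case.
- **Masking with A/B labels would not cure selection on a two-sided p-value.** Correct, and it determines the form of the fix.

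**Conclusion.** The point holds as a weakness in a stated rule. Section 17a excludes everyone but participants from masking, one team collects and analyses, the stored code shows the arm, and the covariates and multiplicity method are open. Arm-aware analysis choices are therefore possible under the plan as written. This rests on reading the randomization code in section 19 as the number in section 16a, which the description of the envelopes supports.

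The size cannot be derived from the documents. The simulated 9% to 17% shows what free covariate choice guided by significance could do under assumed correlations. It is not an estimate for this trial, and it is not the amount that masking by A/B labels would save. A reader might infer that a relabelled file returns the error rate to 5%; it does not. For heart rate variability and skin response, the consequence is limited to how the stimulation check and the validation of PANAS-N are read.

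This should be changed because the remedy is cheap, although the masked self-rating already protects the outcome measurement.

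**What to change.** Amend sections 17a and 5d to state that data processing and analysis are masked, in this order:

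1. The team member who generated the sequence prepares the Qualtrics and iMotions exports, removes the randomization code and any arm variable, and replaces study numbers with random IDs.
2. On this pooled file, which has no arm column, the team fixes and locks the ECG and skin-response processing, the covariates, the model code and the multiplicity method.
3. Only then is the allocation merged, first as A and B, and the locked primary analysis is run. The key to A and B is released afterwards.

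Session staff still know the arms, and nothing changes for participants. The cost is the key-holder's time to prepare the export. In addition, the PI-only access to the iMotions recordings in section 19 has to be adjusted so that the key-holder can make the export and the signals are processed from it.

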## Procedure for unblinding if needed {17b}

In the event of an emergency, the investigator is to decide the necessity of unblinding the subject’s treatment assignment. If unblinding occurs, the investigator must record the reason for unblinding, as well as the date and time of the unblinding.

## Data collection and management

### Plans for assessment and collection of outcomes {18a}

#### Data collection

A Qualtrics Survey [31] module will be the electronic case report form (eCRF) and used as the source document for the anamnestic information collected at the screening and for all the baseline and subsequent assessments and evaluations with the exceptions of the two diagnostic interviews MINI and SCID-5-PD, that will be administered by the investigator in paper format.

#### Screening

The screening procedure will be completed at the lab after the informed consent is signed and before the study procedure will start, to check the eligibility to the study and collect background information that will be used to analyze and interpret the study results. The following information will be collected and recorded: Demographics (date of birth, gender), Medical History (details of any history of disease or surgical interventions), Concomitant Medication (all over-the-counter or prescription medication, vitamins, and/or herbal supplements); Physical Examination (height, weight, and oral temperature; resting pulse and blood pressure (BP) measurements will be measured after the participant has sat for at least 5 min). Anamnesis of the substances assumed before the procedure (drugs, alcohol, nicotine, caffeine). No blood or urine samples will be collected.

The BPD module of the SCID-5 PD and MINI will be administered to confirm the BPD diagnosis and exclude the diagnosis of bipolar disorder, alcohol or substance use disorder, and history or diagnosis of bipolar or chronic psychotic disorder (e.g., schizophrenia, schizoaffective disorder).

#### Borderline personality disorder general psychopathology

The participants will complete the following additional self-report measures to assess BPD symptoms, self-harm, and emotion dysregulation severity:Difficulties in Emotion Regulation Scale (DERS) to assess difficulties in emotion regulation. The DERS [34] is a 36-item self-report measure of six facets of emotion regulation. Items are rated on a scale of 1 (“almost never [0–10%]”) to 5 (“almost always [91–100%]”). Higher scores indicate more difficulty in emotion regulation [34].Borderline Symptom List (BSL-23) and Borderline symptom list - behavior supplement (BSL-SUPP) to quantify symptoms and behaviors associated with BPD. The Borderline Symptom List – Short Version (BSL-23) is a 23-item self-rating instrument for specific assessment of borderline personality disorder (BPD) symptomatology in adults (18+). The scale assesses DSM BPD diagnostic criteria (e.g., affective instability, recurrent suicidal behavior, gestures, or threats, or self-mutilating behavior, and transient dissociative symptoms) in addition to items that are based on borderline-typical empirical findings regarding self-criticism, problems with trust, emotional vulnerability, and proneness to shame, self-disgust, loneliness, and helplessness [35]. The BSL-23 has a single factor structure and excellent psychometric properties, with high internal consistency with a Cronbach’s of 0.97 and test–retest reliability of 0.82 within 1 week [36]

#### Self-reported rating measures

The primary outcome will be measured through the PANAS [27]. Before undergoing the taVNS and affect induction procedure, (“baseline” or t1), after 4-min taVNS and before the first video (“preinduction” or t2), and after each video (“postinduction” or t3, t4, t6, and t8), participants will be asked to provide affect ratings using the 20-item PANAS [27] (Table 1). The scale uses adjectives that describe mood states rather than discrete emotions and are rated from 1 = very slightly or not at all to 5 = extremely. The PANAS is used widely in mood induction procedures because of its good validity and test–retest reliability. At postinduction, participants provided self-report ratings on six basic emotions felt in response to each video (disgust, fear, anger, sadness, happiness, and surprise) on a scale from 1 = not at all to 7 = extremely. A total of 4 min after each negative video, participants provided another set of PANAS ratings to measure changes in mood over a longer period (“recovery” or t5, t7, and t9). The PANAS is a reliable and valid measure of the construct it is intended to assess [37].

Moreover, participants will be asked during postinduction about their perceived effectiveness in managing their emotions (PEME) by asking them to rate “How difficult was it to manage your emotional response to this film clip?” from 1 = not at all to 9 = extremely. This scale will be interpreted as a subjective difficulty in regulating emotions in response to each video stimulus.

#### Physiological measurements

During the entire procedure, continuous ECG recording in a sitting position and a GSR will be performed using IMotions software [32] to integrate the sensors’ data with the affect-induction procedure and the self-reported measures.

For the ECG recording, a 3-electrodes Shimmer 3 ECG device will be used. The electrodes will be placed at the right arm, right leg, and left leg. The ECG recording will be used to measure the HRV variability as a potential indicator of actual stimulation of the vagus nerve in the taVNS group and as an additional and indirect measure of emotion regulation in both groups.

For the recording of electrodermal activity (EDA, also known as galvanic skin response; GSR), recording will use a 2 electrodes Shimmer GSR device. The GSR electrodes will be placed on the volar phalanges of the fingers (proximal, medial, or distal) on the palms of the non-dominant hand. The GSR will be used to give an additional objective physiological measure of emotional arousal/intensity that in our hypothesis will parallel the PANAS ratings given by the participants.

#### Participation Quality Evaluation

After the completion of the stimulation procedure and assessment, the following additional questions will be administered to participant to evaluate the quality of their participation (Participation Quality Evaluation or PQE): *To what extent did you empathize with the characters in the film? (Repeated for all the four videos); Did you close your eyes during any of the videos in this part of the experiment? Did you feel extremely uncomfortable with regards to the content in the videos? Did you feel that you let yourself experience the emotions that you were experiencing? Was it difficult to do this because someone else was in the room with you? Had you seen any of the video clips used in this study before? How was your attention during the procedure? Was there anything distracting? Were there other barriers to your participation? Is there anything that could be improved or done to reduce your burden? Do you want to leave some other comments on something that you think is worthwhile or important?*

### Plans to promote participant retention and complete follow-up {18b}

The study was designed to minimize as much as possible the burden for the participants. The entire procedure will be completed in a period of two hours during which the investigator will always be present in the room to assist the participant with all potential problems or difficulties experienced. In case of discontinuation of participation for any reason, the participant will be asked to complete the PQE (see above) to further assess the reasons for discontinuation if not directly expressed by the participant or evident to the investigator. A follow-up visit will be offered to the participant in case of discontinuation due to AE.

### Data management {19}

eCRF entries will be considered source data since the CRF is the site of the original recording (e.g., there is no other written or electronic record of data). In this study, the Qualtrics Survey module will be the eCRF and will be used as the source document for the anamnestic information collected at the screening and for all the assessments and evaluations.

All study data will be entered on the online Qualtrics Survey. Data will be protected in accordance with the “Qualtrics Security statement” (SOC 2 Type II Certification, ISO 27001, 27017, and 27018 Certifications, FedRAMP Authorization, HITRUST), and access available only to the research group. The data will be stored in the online Qualtrics Account owned by to the Principal Investigator (PI) and protected by a unique password.

The participants will be identified by a unique sequential study-specific participant ID number and a unique randomization code. These two numbers will be recorded in the participant module in the IMotions software [32] and on the first page of the online Qualtrics Survey [31]. The name and any other identifying detail will NOT be included in any study data electronic file and no key between participant ID number, name, or other information that could identify the participant will be used. The data recorded in the IMotions software will be stored off-line in a dedicated computer, protected by a password that only the PI has access to.

All the other documents (informed consent, envelope with participant number and randomization code, MINI, and SCID 5 PD) will be stored in a locked cupboard at the lab accessible only to the PI. On all study-specific documents, other than the signed consent, the participant will be referred to by the study participant number/code, not by name.

